## Abstract

**Introduction:**

Acute peripheral arterial occlusions can be treated with intra-arterial catheter-directed thrombolysis as an alternative to surgical thromboembolectomy. Although less invasive, this treatment is time-consuming and carries a significant risk of haemorrhagic complications. Contrast-enhanced ultrasound using microbubbles could accelerate dissolution of thrombi by thrombolytic medications due to mechanical effects caused by oscillation; this could allow for lower dosages of thrombolytics and faster thrombolysis, thereby reducing the risk of haemorrhagic complications. In this study, the safety and practical applicability of this treatment will be investigated.

**Methods and analysis:**

A single-arm phase II trial will be performed in 20 patients with acute peripheral arterial occlusions eligible for thrombolytic treatment. Low-dose catheter-directed thrombolysis with urokinase will be used. The investigated treatment will be performed during the first hour of thrombolysis, consisting of intravenous infusion of 4 Luminity phials (6 mL in total, diluted with saline 0.9% to 40 mL total) of microbubbles with the use of local ultrasound at the site of occlusion. Primary end points are the incidence of complications and technical feasibility. Secondary end points are angiographic and clinical success, duration of thrombolytic infusion, treatment-related mortality, amputations, additional interventions and quality of life.

**Ethics and dissemination:**

Ethical approval for this study was obtained in 2015 from the Medical Ethics Committee of the VU University Medical Center, Amsterdam, the Netherlands. A statement of consent for this study was given by the Dutch national competent authority. Data will be presented at national and international conferences and published in a peer-reviewed journal.

**Trial registration numbers:**

Dutch National Trial Registry: NTR4731; European Clinical Trials Database of the European Medicines Agency: 2014-003469-10; Pre-results.

Strengths and limitations of this studyThis will be a first in man study to examine the safety and technical feasibility of therapeutic microbubbles, combined with the application of ultrasound and catheter-directed thrombolysis in peripheral arterial occlusions.This is a ‘single-arm’ trial. The data will be used to inform a future large multicentre randomised controlled trial comparing conventional catheter-directed thrombolysis with Microbubble and UltraSound-accelerated Thrombolysis.The present study is a non-randomised phase II trial; therefore, the results cannot confirm benefit of sonothrombolysis for peripheral arterial occlusions, only safety and feasibility is analysed.The present study does not compare other thrombolysis techniques or protocols.

## Introduction

Acute limb ischaemia can be caused by a thrombus occluding an artery in an arm or leg. This is an emergency situation that can result in amputation or death if not treated successfully.^1^ Intra-arterial infusion of thrombolytic agents, that is, catheter-directed thrombolysis, can restore blood flow by dissolving the clot, as a less invasive alternative to surgical thromboembolectomy.^2^ In comparison with the lysis of small arterial occlusions in patients with myocardial infarction, larger peripheral arterial occlusions require higher doses of lytic agents and infusion over a longer period of time. Inevitably, such treatment is accompanied by a risk of major haemorrhagic complications, such as haemorrhagic stroke, in up to 8% of patients.^3^ Furthermore, this technique is time-consuming (several days of bed rest is usually required) and repeated angiography for treatment monitoring is needed, putting patients at risk for contrast-induced nephropathy. As a result, this leads to high morbidity rates and a significant patient burden. Methods to improve this therapy are therefore highly sought after.

A potential accelerator of thrombolytic therapy is contrast-enhanced ultrasound. Contrast agents, consisting of 5–10 µm gas-filled particles (microbubbles), have initially been used as diagnostic ultrasound contrast enhancers. A new field of research investigates these agents for potential therapeutic purposes such as targeted drug delivery and thrombolysis.^4^ The proposed mechanism of action in thrombolysis is that microbubbles can oscillate under the influence of ultrasound. At high intensities, this oscillation can lead to microbubble collapse and the production of mechanical forces on the clot surface, making the thrombus more susceptible to thrombolytics, thus accelerating thrombolysis.^5^

In early stages of clinical research, this technique has been shown to be efficient as treatment for acute cerebral stroke and acute myocardial infarction.^6 7^ Although the safety of their clinical administration in treating smaller arteries in the heart has been a topic of discussion in the past, postmarketing data for diagnostic indications showed continued safety after extensive research in more recent years.^8–10^ For therapeutic thrombolytic purposes, this technique has been shown to be effective and safe in a porcine model of large peripheral arterial occlusions.^11^ In this study, we will investigate the therapeutic application of microbubbles with ultrasound in combination with catheter-directed thrombolysis for patients with peripheral arterial occlusions. An illustrative video regarding our research project is available as online supplementary video.

10.1136/bmjopen-2016-014365.supp1Supplementary material 1

## Methods and analysis

### Study objectives

To investigate the safety and practical applicability of the therapeutic application of microbubbles and ultrasound in combination with catheter-directed thrombolysis for patients with peripheral arterial occlusions.

### Design

The Microbubbles and UltraSound-accelerated Thrombolysis (MUST) trial is a single-arm phase II trial.

### Primary study parameters

Main end points will be the safety and technical feasibility of the experimental treatment. Safety will be determined by treatment-related mortality, the occurrence of adverse events (AEs), serious adverse events (SAEs) and suspected unexpected serious adverse reactions (SUSARs). AEs will be defined as any undesirable experience occurring to a subject during the experimental treatment period, whether or not considered to be related to the investigational drug or intervention. SAEs will be defined as any untoward medical occurrence or effect that at any dose results in death; is life threatening (at the time of the event); requires hospitalisation or prolongation of existing in-patients’ hospitalisation; results in persistent or significant disability or incapacity; is a new event of the trial likely to affect the safety of the subjects, such as an unexpected outcome of an adverse reaction. SUSARs, which are related to the microbubble infusion and ultrasound application, are the formation of microemboli resulting in occlusion of the microcirculation, haemorrhages, hypotension, heart rhythm disorders and anaphylaxis. See the section ‘Adverse events’ for detailed handling procedures of AEs, SAEs and SUSARs. Haemorrhagic complications related to thrombolytic therapy will be reported according to the Standardized Bleeding Definitions for Cardiovascular Clinical Trials proposed by Mehran *et al*.^12^

Technical feasibility will be defined as accomplishment of the experimental protocol during the first hour of thrombolysis.

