### Study procedures

#### Intervention

A flow chart of the patient work-up after presentation in our hospital is presented in figure 1. Low-dose thrombolytic treatment with urokinase (UK) will be initiated following our standard institutional protocol: a catheter is placed intra-arterially in the affected artery and a bolus injection of 500 000 International Units (IU) of UK (Medacinase Urokinase, Medac, Hamburg, Germany) will be followed by the continuous infusion of 50 000 IU of UK per hour and 9600 IU of heparin per 24 hours. The experimental treatment consists of (in addition to the standard thrombolytic therapy) the use of local 1.8 MHz transdermal ultrasound (Philips iE33 Ultrasound Machine, Eindhoven, the Netherlands), and the intravenous infusion of 4 Luminity phials (total 6 mL, diluted with saline 0.9% to 40 mL total, Lantheus MI UK, Newbury, Berkshire, UK) during the first hour of thrombolysis with U. An ACIST VueJect (Bracco Imaging Europe B.V., the Netherlands) infusion pump will be used to infuse the four phials continuously. Ultrasound will be intermittently activated (3 s manual flash to burst microbubbles with Mechanical Index (MI) 1.08 (pulse duration 20 μs, frequency 1.8 MHz, frame rate 39 Hz), 7 s of visualisation of inflow of the microbubbles at MI±0.11), at the site of occlusion during the first hour of thrombolysis. Criteria for discontinuation of the experimental treatment during the first hour will be the occurrence of any AEs potentially related to the experimental treatment, such as bleeding and allergic reactions.

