### Adverse events

AEs will be recorded in detail in the electronic patient record. Any SAEs that occur after joining the trial will be reported to the accredited Medical Ethics Committee of our institution according to national and institutional guidelines. All AEs will be followed up until they have abated or until a stable situation has been reached. Depending on the event, follow-up may require additional tests or medical procedures as indicated and/or referral to a general physician or medical specialist. An interim analysis after 10 patients will be performed. If SAEs in these 10 patients have occurred, we will discuss the continuation of the study. The study will be prematurely terminated if two or more intracranial bleedings occur or more than five allergic reactions.

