## Discussion

The MUST trial is a phase II single-arm clinical trial. In this study, the safety and feasibility of an experimental ultrasound technique will be investigated for the first time in patients with large peripheral arterial occlusions.

We believe that this procedure is safe and can accelerate thrombolysis, thereby allowing for reduction of thrombolytic dosage, which in turn reduces the risk of major haemorrhagic complications.

An experimental bolus therapy with microbubbles and ultrasound could accelerate thrombolysis because at high ultrasound intensities microbubbles can collapse, resulting in mechanical forces on the clot surface. The formation of small channels in the thrombus leads to exposure of a larger total surface susceptible to thrombolytics.^5^

In regard to the therapeutic application of contrast agents, several studies have been performed in patients with ischaemic stroke and myocardial infarction. A systematic review of sonothrombolysis shows that this treatment option improves short-term and long-term clinical outcomes, while potentially reducing bleeding risk, in patients with ischaemic stroke.^13^ Nevertheless, dose escalation studies show that the safety (in terms of bleeding and microemboli) needs to be further investigated before enrolling patients in phase III trials.^14^ Few and heterogeneous studies examined the therapeutic application of sonothrombolysis in patients with myocardial infarction. Although pilot studies affirm safety and feasibility, the application of therapeutic ultrasound with longer pulse durations (20 vs 5 μs) was reported to result in unexpected coronary vasoconstriction in a recent clinical trial.^15^

Potential reported mechanisms for this effect are the summative effect of myocardial ischaemia, reperfusion damage and long-pulse-duration sonoporation on endothelial damage, all leading to calcium overload.

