In regard to Luminity contrast agent dose regimens, the recommended dose for diagnostic indications is 1.3 mL dispersion added to 50 mL of sodium chloride 9 mg/mL (0.9%) or glucose 50 mg/mL (5%) solution injected over a short time period.^18^ For therapeutic purposes, in large peripheral arteries there are no dose studies available. However, in our university hospital the Sonolysis study has been performed by our Cardiology department to treat acute ST elevation myocardial infarction patients with Luminity microbubbles and high mechanical ultrasound.^19^ The dose used was one flacon Luminity of 1.5 mL which contains 225 μL perflutren diluted with 48.5 mL of saline 0.9% to create a 50 mL suspension. Patients were treated for 15 min with an infusion rate of 200 mL/h. No SAEs occurred. In the present study to establish a therapeutic effect in large arterial occlusion, we will also infuse one phial per 15 min but we will treat patients for 60 min. We will use four flacons of 1.5 mL Luminity containing 900 μL perflutren diluted with saline 0.9% to 40 mL total volume to be infused during 1 hour. The clinical consequences of overdose with Luminity are not known. Single doses of up to 100 μL dispersion/kg and multiple doses up to 150 μL dispersion/kg were tolerated well in phase I clinical trials.^20^ This equals to the infusion of 12 mL (eight flacons) of Luminity dispersion. We will administer a total of 6 mL (four flacons) of Luminity dispersion. Furthermore, we will not administer them as single bolus doses but as low-speed continuous infusion. During the experimental protocol with microbubble infusion, patients will be continuously monitored.

As with all contrast agents, the risk of anaphylactic reactions to contrast remains. Therefore, administration of contrast agents in a centre with full resuscitation possibilities is mandatory. Furthermore, during the first hours of administration, monitoring of vital parameters of patients is important.

In this study, thrombolysis is performed with the fibrinolytic urokinase, which is the most used fibrinolytic agent for the treatment of peripheral arterial occlusions worldwide and is standard care in the Netherlands. Some countries use tissue plasminogen activator for this indication. A Cochrane review on the topic states that there is no evidence that (r)t-PA is more effective than urokinase for patients with peripheral arterial occlusion.^21^

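### SUSARs, part of the primary safety end point, are defined as a closed list of five pre-named reactions with no test of seriousness or unexpectedness

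*Protocol article*

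**What the plan says.** The Primary study parameters section determines safety from treatment-related mortality, AEs, "serious adverse events (SAEs) and suspected unexpected serious adverse reactions (SUSARs"). It defines AEs and SAEs by criteria. An AE is any undesirable experience during the experimental treatment period, whatever its cause. An SAE is an event meeting one of the usual seriousness outcomes, or a new event in the trial that bears on subjects' safety.

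SUSARs are handled differently: "SUSARs, which are related to the microbubble infusion and ultrasound application, are the formation of microemboli resulting in occlusion of the microcirculation", and then "haemorrhages, hypotension, heart rhythm disorders and anaphylaxis". The verb is a plain 'are', with no wording that leaves the list open. The paragraph then deals separately with bleeding due to thrombolytic therapy, which is to be reported under a published set of standardised bleeding definitions. For the handling of all three event classes it refers the reader to the Adverse events section.

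**The concern.** A SUSAR has to be suspected, unexpected and serious. A list fixed before the first patient is treated names what the investigators already expect, so it cannot also serve as the class of unexpected reactions. The list also says nothing about seriousness.

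What is at stake is the meaning of one named component of the primary safety end point. The study is described as first in man, has one arm and 20 patients, and is meant to support a later randomised trial. With no control group, readers depend on event classification to tell a new reaction to microbubbles and ultrasound from a known one. A SUSAR line built on this definition would not make that distinction.

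**Working it through.** The article states no SUSAR rate or threshold, so there is no figure to reproduce. The check sets the definition against the rest of the article.

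**1. Are the listed reactions treated as anticipated elsewhere?**

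- Bleeding and allergic reaction: the Intervention section lists as grounds for discontinuation "any AEs potentially related to the experimental treatment, such as bleeding and allergic reactions". This ties both to the experimental treatment, not only to urokinase.
- Intracranial bleeding and allergic reaction: the Adverse events section says "The study will be prematurely terminated if two or more intracranial bleedings occur or more than five allergic reactions".
- Bleeding and microemboli: the Discussion says of sonothrombolysis in stroke that "dose escalation studies show that the safety (in terms of bleeding and microemboli) needs to be further investigated".
- Anaphylaxis: the Discussion says "As with all contrast agents, the risk of anaphylactic reactions to contrast remains".
- Hypotension and heart rhythm disorders: I found no separate statement that these are expected reactions. They are anticipated only in the sense of being listed in advance.

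Three of the five are therefore documented as foreseen in other sections.

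**2. Does anything else in the article supply the missing criteria?** No. The Adverse events section, to which the definition points, covers AE recording, SAE reporting, the interim look and early termination. It does not mention SUSARs. The closed list is the only operative SUSAR text shown.

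**3. How would hypothetical events be classified?** The last column requires an event to be serious, suspected to be related to microbubbles or ultrasound, and not consistent with the reference safety information (RSI).

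| Event | SUSAR on the literal text? | SUSAR by the three elements? |
|---|---|---|
| Brief, non-serious hypotension judged related to the infusion | Yes | No |
| Serious anaphylaxis judged related, assumed consistent with the RSI | Yes | No |
| Serious listed reaction judged related, not consistent with the RSI | Yes | Yes |
| Serious unlisted reaction judged related, not consistent with the RSI | No | Yes |
| Serious bleed attributed to urokinase alone | No | No |

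Rows 1 and 2 are false inclusions and row 4 is a false exclusion, so the label errs in both directions. The row 4 event still meets the SAE definition, and the Adverse events section sends SAEs to the ethics committee. The row 5 event is classified correctly by the present text, because the SUSAR sentence is confined to reactions related to microbubbles and ultrasound.

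**The case against.** Several objections have force.

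*Thrombolytic bleeding does not enter the SUSAR count.* This stands. The Introduction says that "such treatment is accompanied by a risk of major haemorrhagic complications, such as haemorrhagic stroke, in up to 8% of patients". A reader might apply that to this trial: 20 × 0.08 = 1.6 expected events, and 1 − 0.92^20 = 0.81 for at least one. The reader might then infer that the SUSAR count will be inflated by about that much. The text does not support this. The 8% is an upper figure for thrombolysis in general, the SUSAR sentence requires a relation to microbubbles and ultrasound, and thrombolytic bleeding has its own reporting scheme. The share of bleeds that would be attributed to the experimental component is not given, so these numbers do not measure SUSAR inflation.

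*New reactions would not be missed.* This also stands. A reader might infer that an unlisted serious reaction disappears from the safety data. It does not: it remains an SAE, SAEs are themselves part of the primary safety end point, and they are reported.

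*Vasoconstriction is not a good example of an omitted reaction.* A reader might cite the Discussion's report of unexpected coronary vasoconstriction at a 20 μs pulse duration, which is also used here. The Discussion goes on to describe vascular spasm in peripheral treatment as normal and harmless to the patient. On that view it would be neither unexpected nor serious here, so it does not illustrate the gap.

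*Seriousness may be carried by the term itself.* This is a possible reading, and it would remove row 1 of the table. The same reading would also import unexpectedness, which is what a list of foreseen reactions contradicts. It would not admit row 4 either.

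*An article condenses, and expectedness is judged against product information not shown here.* The absence of that information is no finding. The article does state a definition, however, and the definition as stated is wrong.

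*No decision depends on it.* This stands and limits the weight of the point. The sample-size rationale refers to toxic effects or SAEs below 20%, the interim look to SAEs, and termination to intracranial bleeding and allergic reactions.

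**Conclusion.** The definition is wrong as written. It contradicts the term it defines and the article's own account of which reactions are foreseen. Followed literally, it gives a SUSAR count that can be too high (expected or non-serious listed reactions judged related) and too low (serious, unexpected, unlisted ones).

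The severity is minor. The effect is misclassification within the safety reporting, with no loss of events and no change to any stated decision rule. Its numerical size cannot be estimated from the document, because no rate is given for reactions attributed to microbubbles or ultrasound.

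The conclusion assumes that the list is closed, as its wording indicates, and that the full protocol does not replace it with a criteria-based definition.

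**What to change.** In Primary study parameters, define a SUSAR as a reaction that is (a) serious by the SAE criteria already given, (b) suspected to be related to microbubbles or ultrasound, and (c) not consistent with the reference safety information.

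Relabel the five reactions as adverse events of special interest. Tabulate them separately from SUSARs, whatever their seriousness, and record for each its relatedness to urokinase and to microbubbles or ultrasound. A listed reaction can still be a SUSAR if it meets all three conditions.

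The cost is revised wording and one relatedness field on the case report form. No dose, schedule, sample size or stopping criterion is affected.

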### Secondary study parameters

Angiographic success will be defined as dissolution of >95% of the thrombus with outflow to at least one crural artery. Clinical change/success will be reported according to Rutherford’s recommended scale for gauging changes in clinical status (table 1). Amputations will be defined as either major (above or below knee amputation) or minor (metatarsal or toe amputation). Additional interventions will be categorised as either surgical (eg, thromboembolectomy, bypass graft surgery) or percutaneous (percutaneous transluminal angioplasty, stent placement) and as either required for restoration of patency or necessary for correction of underlying lesions. We will also determine microcirculation of the limb (by Laser Doppler measurements, Perimed Instruments, Järfälla, Sweden), 30-day mortality, conversion to surgery, serum fibrinogen concentrations measured during thrombolytic treatment on a daily basis, pain by visual analogue scale (VAS) and quality of life by SF-36 questionnaires. The duration of thrombolysis will be defined by the time span between initiation and completion angiography.

**Table 1 T1:** Rutherford’s^24^ recommended scale for gauging changes in clinical status

+3	Markedly improved: no ischaemic symptoms and any foot lesions completely healed; ABI essentially ‘normalised’ (increased to >0.90)
+2	Moderately improved: no open foot lesions; still symptomatic but only with exercise and improved by at least one clinical chronic ischaemia category; ABI not normalised but increased by >0.10
+1	Minimally improved: >0.10 increase in ABI* but no categorical improvement or vice versa (ie, upward categorical shift without an increase in ABI of >0.10)
0	No change: no categorical shift and <0.10 change in ABI
−1	Mildly worse: no categorical shift but ABI decreased >0.10 or downward categorical shift with ABI decrease <0.10
−2	Moderately worse: one category worse or unexpected minor amputation
−3	Markedly worse: more than one category worse or unexpected major amputations

*In cases where the ABI cannot be accurately measured, an index based on the toe pressure, or any measurable pressure distal to the site of revascularisation, may be substituted.

ABI, Ankle Brachial Index.

Adapted from Rutherford RB et al. JVS 1997.

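### The headline mortality and graded-bleeding results depend on attributing cause, which this single-arm design cannot do reliably, and treatment-related mortality is primary in one place and secondary in another

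*Protocol article*

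**What the plan says.** Primary study parameters opens the safety end point with "Safety will be determined by treatment-related mortality", followed by AEs, SAEs and SUSARs. Haemorrhage is then named twice in that section, each time with a cause attached:

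- as a reaction to the experimental component: "SUSARs, which are related to the microbubble infusion and ultrasound application, are the formation of microemboli resulting in occlusion of the microcirculation, haemorrhages";
- as a complication of lysis: "Haemorrhagic complications related to thrombolytic therapy will be reported according to the Standardized Bleeding Definitions for Cardiovascular Clinical Trials".

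Other parts of the same section carry no causal condition. AEs count "whether or not considered to be related to the investigational drug or intervention", though only during the experimental treatment period, whose length is not given. SAEs are defined by outcome, death included.

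Under Intervention, standard lysis starts with "a bolus injection of 500 000 International Units (IU) of UK", followed by a continuous urokinase infusion of 50 000 IU per hour and heparin. Microbubbles and ultrasound are added during the first hour. The Design section states a single arm.

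On mortality, the abstract (Methods and analysis) reads "Secondary end points are angiographic and clinical success, duration of thrombolytic infusion, treatment-related mortality, amputations". Secondary study parameters lists "30-day mortality, conversion to surgery" and attaches no causal condition to the 30-day figure.

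**The concern.** The trial's main answer is a safety statement, and readers will look first at the death rate and the graded bleeding rate. As worded, both require someone to decide what caused each event. For bleeding, the design gives little basis for that decision. Agents that can cause bleeding act together in the same hour, there is no concurrent control, and the proposed mechanism (Introduction, Discussion) is that microbubbles make the thrombus more susceptible to the lytic. A bleed may therefore reflect the combination.

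Two trials with identical events could report different headline rates because they attributed differently. Separately, an end point that is primary in one section and secondary in another leaves open which death figure belongs to the main result.

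**Working it through.** The plan gives no bleeding or mortality figure to reproduce, so the check sets the definitions side by side and then sizes the effect.

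**Step 1. Which components need a causal judgement?**

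| Component | Causal condition | Window stated |
|---|---|---|
| Mortality (primary) | treatment-related | none |
| AEs | none | experimental treatment period, length undefined |
| SAEs | none | any after joining the trial (Adverse events section) |
| SUSARs, including haemorrhage | related to microbubbles and ultrasound | none |
| Bleeds under the standardised definitions | related to thrombolytic therapy | none |
| 30-day mortality (secondary) | none | 30 days |

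**Step 2. Where does a bleed go?**

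- Serious, any cause: counted as an SAE.
- Non-serious, within the experimental treatment period: counted as an AE.
- Ascribed to thrombolysis, at any time: reported under the standardised definitions.
- Ascribed to microbubbles and ultrasound: on the SUSAR list, with no grading stated.
- Ascribed to neither: no grading stated. If it is also non-serious and later than the treatment period, it has no stated place at all.

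The last gap depends on the length of the period. The article ties the experimental protocol to the first hour, while the Introduction says conventional lysis usually requires several days of bed rest. If the period means that hour, most of the time at risk lies outside it.

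**Step 3. Size.** Inputs: N = 20 (Patients and eligibility criteria); background major haemorrhage up to 8% (Introduction).

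- Expected major bleeds: 20 × 0.08 = 1.6.
- Chance of at least one: 1 − 0.92^20 = 1 − 0.189 = 81.1%.
- Effect of one patient with a bleed on the rate: 1/20 = 5 percentage points.
- Exact one-sided 95% upper bound: 0/20 gives 1 − 0.05^(1/20) = 13.9%; 1/20 gives 21.6%.

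**Step 4. Illustration, on assumed rates.** Suppose the true rate is 16% and half the bleeds are ascribed elsewhere, so that the attributed rate is 8%. The chance that the attributed count is zero rises from 0.84^20 = 3.1% to 0.92^20 = 18.9%. At 24%, with half ascribed elsewhere, it rises from 0.76^20 = 0.4% to 0.88^20 = 7.8%. The 16%, the 24% and the one-half are assumptions, and only the attributed count is affected.

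**Step 5. Could the event rate itself supply the attribution?** Hardly. Flagging excess bleeding at 4 or more patients in 20 gives a false alarm in 7.1% of trials at a true 8%. It detects a true 16% with probability 40.1% and a true 24% with probability 74.3%.

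**The case against.** The strongest reply is that the primary safety end point already contains cause-free components. AEs count regardless of relation, SAEs include every death and serious bleed, 30-day mortality is recorded, and the rules in the Adverse events section (the interim look at SAEs and the stop for intracranial bleeding) have no causal condition. This stands. A reader might infer that a death or bleed ascribed to urokinase or to the disease disappears from the safety record. The documents do not support that.

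Second, the article does not say that bleeds ascribed elsewhere go ungraded. Every patient receives urokinase and heparin, so all bleeds could be read as related to lysis. Likewise, treatment could mean the combination, as the study objective suggests. Both readings are possible, but neither is stated. The separate listing of haemorrhage under microbubbles pulls against the first, and under the second a death ascribed to underlying disease would still fall outside the headline figure.

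Third, it would be too strong to say that no event can ever be assigned to a component. Anaphylaxis is on the microbubble list and might be attributable. The difficulty concerns bleeding chiefly.

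Fourth, the article acknowledges the lack of a control and explains the absence of an independent committee. A condensed article may also leave the causality procedure to the full protocol. None of these is counted here as a fault.

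**Conclusion.** The point holds as a limited one. The headline mortality and graded-bleeding figures depend on a causal judgement that the design supports poorly for bleeding. Grading is not stated for bleeds ascribed to microbubbles or to neither component. A late non-serious bleed may go uncounted, depending on how the experimental treatment period is read. The level of treatment-related mortality is a plain contradiction between the abstract and Primary study parameters, whatever view is taken of attribution.

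The size is 5 percentage points per patient reclassified, with 1.6 major bleeds expected if the 8% applies. That 8% is the article's upper figure, so 1.6 is at the high end of the stated background. The 81.1% is the chance of any major bleed at that rate; it should not be read as the chance of a hidden one. Major bleeds that meet the SAE criteria are counted in any case. This is an inexpensive improvement to the reporting of safety and does not show that harm would be concealed.

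**What to change.** In Primary study parameters:

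1. Replace treatment-related mortality with all-cause 30-day mortality, which Secondary study parameters already collects.
2. Report all haemorrhages whatever the presumed cause, each graded by the bleeding definitions already cited.
3. State one window for this count, covering the whole of thrombolysis.
4. Keep presumed cause as a descriptive column.

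Then align the abstract with that section so that mortality has one level throughout.

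The cost is mostly wording. Two things are not free: the reported rates may be slightly less favourable, and non-serious bleeds must be recorded through the whole stated window, which the present AE definition does not clearly require. Cause-free reporting will not tell the sponsor how much bleeding the microbubbles add. It gives a figure that does not depend on answering that question.
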